### Trial status

The trial opened to recruitment on the 12 November 2014. The first patient was randomised on the 19 November 2014. The trial was closed to enrolment on the 31 May 2016. The target of 4460 patients was reached. The programme grant completes on 30 April 2019.

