#### Objectives

The objective of the ISDR RCT is to evaluate the safety, acceptability and cost-effectiveness of personalised screening in a whole population setting. The main aim is to assess the relative safety of variable-interval screening as measured by attendance rate. We will test the hypothesis that the difference in attendance rates between the two pathways is within an acceptable equivalence margin.

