### Intervention, assessments and procedures

The ISDR DW is a relational database that stores both the data and how the data are related. The Liverpool GPs gave permission for their PWD to be directly contacted to give permission for the data held in primary care relating to their diabetes to be transferred to the DW. The DW was established to collate and dynamically link individual risk factor data from GP practices, STDR outcome data from the DR assessment clinic at St Pauls Eye Unit and the LDESP screening software (OptoMize). This central data repository was used to develop the locally applicable RCE described above using a continuous Markov model.

The RCE was developed using routinely collected primary and secondary care data from 11 806 PWD (46 525 screening episodes) in the LDESP. A detailed description of the RCE has already been published.^30^ In brief, the final covariates for the RCE were selected using a three-step decision process. A number of risk factors for developing STDR were identified in the published literature and in preliminary work in Liverpool. These potential covariates were reviewed by the clinical team and the PPI group, and potential additional covariates were suggested. Potential covariates with a missingness rate of less than 20% in the DW were identified. Then a statistical evaluation of the predictive value of each remaining covariate was undertaken. The covariates selected were disease state (current retinopathy levels in both eyes); age; duration of diabetes; glycated haemoglobin; systolic blood pressure; and total cholesterol. The results suggested that implementing personalised risk-based intervals would reduce the number of screen episodes by 30%.

Our PPI group defined the degree of risk (up to 2.5% risk of developing screen positive DR) acceptable to PWD, allowing assignment of individuals to screen intervals at the time points 6, 12 or 24 months. The choice of these intervals was based on a review of the available literature, our data and consensus between the PPI and research teams. Following each negative screening outcome, individuals are assigned to the longest recall period up to 24 months at which their risk estimation would not exceed the 2.5% threshold.

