### Study visits and assessments

At each follow-up visit, PWD randomised to the personalised risk-based screening arm have their risk recalculated and the next recall interval determined accordingly.

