### Health economics

Table 2 shows the trial intervention diagram.

**Table 2 T2:** Trial intervention diagram

Procedures	Screening	Baseline	Randomisation	Follow-up schedule						Study completion	Premature discontinuation
				6 months*	12 months*	18 months*	24 months*	30 months*	36 months*		
Signed consent form	*X*										
Visual acuity (logMar)		*X*		*X*	*X*	*X*	*X*	*X*	*X*		
Visit questionnaire		*X*									
QoL questionaire† (HUI3 and EQ5D)		*X*		*X*	*X*	*X*	*X*	*X*	*X*		
Assessment of eligibility criteria	*X*	*X*	*X*								
Randomisation			*X*								
Digital imaging		*X*		*X*	*X*	*X*	*X*	*X*	*X*		
Acceptability questionnaire									*X*		

*PWD are randomised to two arms. In one arm, individuals attend at 12-month intervals. In the other arm, individuals attend at 6, 12 or 24 monthly intervals.

†The EQ-5D-5L and HUI3 data will be collected on around 700 eligible PWD and repeated at each visit for those individual PWD. Data will be stratified to balance equal numbers of PWD in each arm and representation from all screening sites.

HUI3, Health Utilities Index Mark 3; QoL, quality of life; PWD, people with diabetes.

A health economics questionnaire, incorporating the health-related quality of life (QoL) questionnaires EQ-5D-5L (an instrument to meaure health state developed by the EuroQol group)^35^ and Health Utility Index 3 (HUI3)^36^ and a bespoke visit questionnaire,^37^ was completed by the first 868 eligible PWD enrolled into the study (a minimum of 700 PWD was required to provide sufficient data). The QoL questionnaires are repeated at every subsequent follow-up visit for those PWD who completed it at baseline.

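### The acceptability questionnaire is scheduled once, at 36 months, when participants who stay on 24-month recall have no visit but every annual-arm participant does

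*Protocol article*

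**What the plan says.** Under Objectives, the protocol article says that the trial is to "evaluate the safety, acceptability and cost-effectiveness of personalised screening in a whole population setting". Acceptability is also on the list of secondary endpoints, measured with a questionnaire made for this trial.

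The timing is in Table 2, under Health economics. The row labelled "Acceptability questionnaire" carries a single mark. Counting columns, it falls under 36 months, in line with the last mark in the visual acuity, quality-of-life and imaging rows. The 24-month, study-completion and premature-discontinuation cells of that row are empty.

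Every month column refers to a footnote on attendance. For the control arm it reads "In one arm, individuals attend at 12-month intervals"; for the personalised arm, "In the other arm, individuals attend at 6, 12 or 24 monthly intervals". The recall rule, under Intervention, assessments and procedures, is that "individuals are assigned to the longest recall period up to 24 months at which their risk estimation would not exceed the 2.5% threshold". Under Study visits and assessments, personalised-arm participants "have their risk recalculated and the next recall interval determined accordingly" at each follow-up visit, so 24-month recall is not a permanent status.

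**The concern.** The questionnaire time suits the annual schedule but not the longest personalised schedule. The trial was motivated by extending the interval in people at low risk, and the article's Background worries that such people may disengage. Their view of a longer interval is the main thing an acceptability measure has to capture. A single collection point at 36 months, if tied to attendance, reaches those who stay on the longest interval only by accident.

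Two things are at stake. A description of acceptability within the personalised arm would rest on a risk-selected subset. Any comparison between arms would set that subset against the full risk range of the annual arm, so randomisation would no longer protect it.

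**Working it through.** **Inputs.** Questionnaire at 36 months only (Table 2). Intervals of 12 months in one arm and of 6, 12 or 24 months in the other (Table 2 footnote). Interval reset at each follow-up visit (Study visits and assessments). Projected effect on workload: "implementing personalised risk-based intervals would reduce the number of screen episodes by 30" per cent (Intervention, assessments and procedures). Randomised: 4460 at 1:1, so 4460 / 2 = 2230 per arm. The article gives no figure for the share of participants on each interval, so there is no stated result to reproduce.

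**Step 1: who has a visit at 36 months.**

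- Annual arm: 12, 24, 36. Everyone has the visit.
- Stable 6-month or 12-month recall: visit at 36.
- Stable 24-month recall: 24, 48. No visit at 36.

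**Step 2: allow the interval to change.** List every sequence of 6-, 12- and 24-month intervals in which a full 24-month interval has been completed by month 36:

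| Sequence | Visit times (months) | Visit at 36? |
|---|---|---|
| 12-24 | 12, 36 | yes |
| 6-6-24 | 6, 12, 36 | yes |
| 6-24-6 | 6, 30, 36 | yes |
| 24-12 | 24, 36 | yes |
| 24-6-6 | 24, 30, 36 | yes |
| 24-24 | 24, 48 | no |
| 24-6-12 | 24, 30, 42 | no |
| 24-6-24 | 24, 30, 54 | no |
| 6-24-12 | 6, 30, 42 | no |
| 6-24-24 | 6, 30, 54 | no |

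Five of the ten have the visit, but these are patterns and not probabilities. What matters is that each of the five involves a change of interval. Nobody who stays on 24-month recall throughout is among them.

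**Step 3: how many might be on 24-month recall.** Let a, b and c be the shares on 24, 12 and 6 months. Relative to annual screening they generate 0.5, 1 and 2 episodes. Assume that the 30% projection applies to the trial arm and that intervals are stable:

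- a + b + c = 1 and 0.5a + b + 2c = 0.7
- subtracting: 0.5a − c = 0.3, so a = 0.6 + 2c
- c = 0 gives a = 0.60 and b = 0.40
- b = 0 gives 0.6 + 3c = 1, so c = 0.133 and a = 0.867

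The range is 60% to 87% of the arm, or about 0.60 × 2230 = 1338 to 0.867 × 2230 = 1933 people.

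**Step 4: sensitivity to change.** As an illustration, start from the 60% and suppose that one fifth of that group move to shorter recall and all gain a 36-month visit. Then 0.60 × 0.8 = 48% of the arm would still lack one. Movement the other way is also possible: 12-12-24 gives visits at 12, 24 and 48, with none at 36.

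**The case against.** The best counter-argument is that the article never says how the questionnaire is delivered. It ties the quality-of-life instruments to follow-up visits but says nothing similar for acceptability. One mark in the last follow-up column could denote an end-of-study survey sent to everyone, and the full protocol may say so. This stands as a condition on the conclusion. It does not remove the point, because Table 2 lists the item as a procedure in a schedule whose columns are defined by attendance. If delivery is independent of visits, the table should say so.

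A second objection is that the article describes no between-arm analysis of acceptability. That is true, but a summary of the personalised arm alone would suffer from the same selection.

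Three stronger readings are tempting and not supported:

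- A reader might infer that acceptability of the 24-month interval goes wholly unmeasured. Because intervals are recalculated, people with patterns such as 12-24, 6-6-24, 24-12 or 24-6-6 have completed such an interval and have a 36-month visit. Nor are they only people whose risk rose: in 12-24 and 6-6-24 the interval lengthened.
- A reader might take 60% as a minimum share with no 36-month visit. It is a share on 24-month recall, it needs stable intervals, and it comes from a projection made when the risk engine was developed, not from the trial arm.
- A reader might add that "The programme grant completes on 30 April 2019", before the last participants enrolled (31 May 2016) reach 36 months. That date is not stated to be the end of follow-up. With uniform accrual over the 559 days from 19 November 2014, it would touch 31/559 = 5.5% of participants, in both arms alike, so it adds no bias between arms.

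**Conclusion.** The point holds in limited form. As scheduled, and if the questionnaire is completed at visits, the only collection time omits participants who remain on 24-month recall and includes the whole annual arm. Acceptability would then be measured in a selected part of the personalised arm, with the most sustained exposure to the extended interval largely missing.

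The size is not stated in the article. Under the two assumptions in the working (the 30% projection carries over to the trial arm, and intervals are stable), 60% to 87% of the personalised arm would be on 24-month recall; fewer of these would lack a 36-month visit to the extent that their intervals change. The conclusion also rests on reading the mark's column from the layout of the table, which agrees with the other rows.

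Acceptability is a named objective but a secondary endpoint. The attendance endpoint, the sample size and the non-inferiority question on detection are untouched. This is a worthwhile, inexpensive improvement and not a condition for the trial's main conclusion.

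**What to change.** Give the existing questionnaire to all randomised participants in both arms at one common time from randomisation, such as 24 months. Complete it at the screening visit if one falls then, and by post otherwise, so that people with no visit due and non-attenders are also asked. Correct the acceptability row of Table 2 to show the time and the mode of delivery. If the questionnaire is already sent independently of visits, stating that in the table is enough.

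Moving it to the first follow-up visit would not serve as well: that visit falls at 12 months in the annual arm but at 6, 12 or 24 months in the personalised arm, and non-attenders would be missed.

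The cost is a minor amendment to timing, some postage, and possibly a lower response by post than in clinic. Participants already past the chosen time would have to be asked late, and the report should state when each person was asked.

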### Sample size and planned analyses

The primary aim is to assess the relative safety of personalised risk-based interval screening as measured by equivalence in attendance rates. The analysis will test the hypothesis that the difference in attendance rates at the first follow-up between the two pathways is within the acceptable range δ=0.05. If the bounds of the 90% CI for the difference in attendance rate are found to be within the confidence limits (−δ,δ (ie, (−0.05 to 0.05)), the results would support equivalence.

The estimated minimum number of patients required is 3940. With an expected loss to follow-up rate of 6% per year due to death and other exclusion from screening (note that non-attendance is the primary outcome and therefore is not factored here), the target for recruitment (randomised into the trial) was 4460 patients (4460*0.94*0.94=3940).

A secondary aim is to investigate whether personalised screening can be considered as non-inferior in detection of STDR when compared with annual screening. The STDR detection rate predicted for the usual care pathway during the 2-year follow-up is approximately 6%, based on data from the LDESP. The sample size required to address the first question (n=4460 patients randomised with 3940 patients retained after 2 years from baseline) will permit us to test for non-inferiority in STDR detection with a maximum allowable reduction of 1.5% of the personalised care pathway compared with standard care, with 5% significance level and power between 60% and 65%.

We will undertake subgroup analyses to assess differences in attendance rates between the two arms for the three different retinopathy groups (the risk groups will be defined based on the individual baseline estimated risk of developing STDR). A logistic mixed-effects model that takes into account the patient’s covariate information over time (including retinopathy level, HbA1c, systolic blood pressure, total cholesterol, disease duration, and age), and screening clinic (clustered data) will be fitted with attendance (yes/no) at the first screening visit as the outcome variable. The random effects of the model will account for the variability by screening clinic.

Using screening activity data stored in the ISDR DW and information collected from the visit questionnaire and EQ-5D-5L and HUI3 responses, we will estimate the cost per QALY within the study period associated with risk-based and annual screening from an NHS perspective and where possible incorporate a broader perspective. We will present bootstrapped incremental cost-effectiveness ratios and cost-effectiveness acceptability curves to characterise the uncertainty associated with our estimates.

We will apply sensitivity analyses to check the sensitivity of the results on the assumption that missing data are missing at random. Different scenarios for missing data mechanisms will be explored.

## Conclusions

This paper describes the design of an RCT to evaluate the feasibility, safety, acceptability and cost-effectiveness of personalised variable-interval risk-based screening compared with fixed annual interval screening. Safety will be measured by the effect on attendance rates to screening, rates and severity of DR, visual outcomes and impact on general diabetes care. As far as we are aware this is the only study to investigate the impact of implementing personalised screening for DR in a randomised controlled trial.

